#### Intervention A

Appropriate antibiotics and minimal duration of antibiotic treatment are based on recent guidelines [10] after local adaptation by a panel of experts. PCT is used to guide antibiotic treatment (Figure 2). We use fosfomycin (3 g single dose) [40] and trimethoprim-sulfamethoxazole (800/160 mg twice daily) for simple UTIs. Furthermore we use ciprofloxacin orally (500 mg twice daily or 250 mg twice daily if the estimated glomerular filtration rate <30 ml/min/1.73 m2) or ceftriaxone intravenously (2 g daily) for febrile UTIs/pyelonephritis. If known, previous antibiotic resistant profiles are considered. If there is a non-susceptible urine pathogen in the current urine culture the antibiotic therapy is adjusted. In inpatients, antibiotic duration is based on absolute values of PCT and relative decreases of PCT levels and pyuria. In outpatients, the antibiotic duration is based on absolute values of PCT only. PCT and pyuria are measured on admission, and, in hospitalized patients, every other day as long as the patient receives antibiotics for the UTI. Pyuria criteria are derived from local data on female patients with UTIs [15]. PCT cutoffs are derived from data from our recent observational study and after extrapolation from patients with LRTIs and sepsis [36,41,42]. Patients with uncomplicated simple UTIs in the PCT group receive NSAIDs regardless of PCT values for symptom resolution given emerging data [43,44]. In the control group, antibiotic durations are recommended based on guidelines (Figure 2).

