### Statistical considerations

The primary analysis population will be the full analysis set, which includes all patients following an intention-to-treat principle. Every effort will be made to keep the number of losses to follow-up minimal. A sensitivity analysis will be carried out including only patients with evaluable primary endpoint data to assess potential bias due to patients lost to follow-up. Two co-primary endpoints will be used to compare, for Intervention A, the duration of antibiotic therapy and, for Intervention B, the length of physician-led hospitalization. A secondary analysis population, the per-protocol population, will be defined, which excludes major protocol violators. Specifically, patients will be excluded from the per-protocol population if they fulfill any of the following: violation of inclusion or exclusion criteria, not treated according to the trial requirements (that is, overriding of triage recommendations on admission or on day 3 without a pre-specified reason) or lost to follow-up. As a sensitivity analysis, the primary analysis will be repeated on the subset of patients with evaluable outcomes (that is, drop-outs are excluded from this additional analysis) and repeated on the per-protocol population.

To test the two continuous primary endpoints of this two-by-two factorial design study we will use the Mann–Whitney *U* test and calculate a median regression model [54]. We do not expect an interaction between the co-primary endpoints (for Intervention A the duration of antibiotic therapy and for intervention B the length of stay in our study). In our previous studies we showed that the shorter duration of antibiotic therapy in LRTIs did not influence the overall length of stay [41,55]. However, our algorithm for antibiotic guidance is different between inpatients and outpatients, which makes effect modification possible. Therefore we will formally test for an interaction using the median regression model. We are aware that the test for an interaction may result in a false negative due to the low power and the rather small sample size [56,57].

In a second step, the primary endpoint will be explored for association with potential prognostic factors in a median regression model considering potential confounding factors such as: age, sex, UTI subgroup, time to reach stability, co-morbidities, patient preferences and living conditions prior to hospitalization.

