## Discussion

The results of earlier studies by our group provided evidence that antibiotic therapy can be guided in patients with LRTI using PCT cutoff ranges. We recently showed that biomarkers, especially ProADM, are able to predict the outcome for patients with LRTIs [58]. On account of this, we added the ProADM to the widely used CURB65 score, resulting in the CURB65-A score capable of guiding triage decisions [31,35].

In this study we extend our concepts to patients with UTI, which contributed approximately 7% of patients in the previous French multi-center ProRATA study [13]. UTIs, as one of the most common indications for antibiotic therapy [59], provide an ideal opportunity for extrapolating our knowledge from LRTI studies.

In the current guidelines [4,10,19] a crucial point in the determination of the length of antibiotic therapy and whether a patient has to be hospitalized or not, has been the distinction between lower and upper UTI, and this classification is still based on subjective criteria. The first aim of this study is to create evidence-based guidelines, which will allow clinicians to administer tailored antibiotic therapy in uncomplicated as well as in complicated UTIs by using PCT levels and pyuria dynamics. This will help to determine the optimal length of antibiotic therapies and avoid antibiotic overuse.

As shown in a study among a population of frail elderly nursing home residents, 43% of all patients receiving antibiotic treatment for an assumed UTI are over-diagnosed and actually do not require antibiotics [60]. Another large potential for reducing antibiotic use lies in febrile UTI patients, who currently receive at least 7 days of antibiotics according to guidelines.

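### The primary rank test is valid but inefficient: it leaves out simple versus febrile UTI type, a presenting characteristic that the protocol itself links to both primary endpoints

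*Protocol article*

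**What the plan says.** Under Statistical considerations the protocol article fixes the confirmatory analysis: "To test the two continuous primary endpoints of this two-by-two factorial design study we will use the" Mann–Whitney U test, together with a median regression model. No stratification factor or covariate is attached to either.

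The two randomized factors meet in one place: "Therefore we will formally test for an interaction using the median regression model". The reason given is that "our algorithm for antibiotic guidance is different between inpatients and outpatients, which makes effect modification possible".

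UTI type comes in afterwards: "In a second step, the primary endpoint will be explored for association with potential prognostic factors in a median regression model". The candidate factors are "age, sex, UTI subgroup, time to reach stability, co-morbidities, patient preferences and living conditions prior to hospitalization".

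Elsewhere the article treats UTI type as a main determinant of care:

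- **Definitions** separates febrile UTI/pyelonephritis from simple UTI by flank pain, costovertebral angle tenderness or temperature, all available at presentation.
- **Intervention A** gives uncomplicated simple UTI in the PCT group its own path, which does not depend on the PCT value.
- **Intervention B** uses ProADM cutoffs for admission in febrile UTI but not in simple UTI.
- **Discussion** says that current guidelines rest both antibiotic length and the decision to hospitalize on the distinction between lower and upper UTI.

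**The concern.** The two primary endpoints are antibiotic exposure and length of physician-led stay. By the article's own account, UTI type bears on both. For simple UTI one listed option reads "We use fosfomycin (3 g single dose", while the Discussion speaks of "febrile UTI patients, who currently receive at least 7 days of antibiotics according to guidelines". If outcomes differ between the types, a test that pools them counts the difference as noise and gives up power.

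This matters most for Intervention B. The sample size section asks for 112 per arm, but 250 enrolled less the 20% loss given in the Abstract leaves 100 per arm. Power is then about 75% on the plan's own assumptions, so power that can be recovered without recruiting anyone is worth having.

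**Working it through.** **Inputs from the article.** A: 10 versus 8 days, SD 5. B: 6 versus 4.5 days, SD 4. Alpha 5%, power 80%. Enrolment 250 with 20% loss: 250 × 0.8 = 200, or 100 per arm.

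**Inputs that are assumed.** The article gives neither the mix of types nor outcome means by type. I take 30 to 50% simple UTI and gaps of 0, 2 and 4 days between types, and hold the overall SD at the planned value.

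**Step 1: the plan's own figures.** n per arm = 2 × (1.96 + 0.8416)² × (SD/difference)².
- A: 2 × 7.849 × (5/2)² = 98.1, so 99.
- B: 2 × 7.849 × (4/1.5)² = 111.6, so 112.

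Both match, and so do all 12 rows of Table 2 (two-sided 5%).

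**Step 2: unadjusted power at 100 per arm** (normal theory). Power = Φ(difference / (SD × √(2/100)) − 1.96).
- A: Φ(2/0.7071 − 1.96) = Φ(0.868) = 80.7%.
- B: Φ(1.5/0.5657 − 1.96) = Φ(0.692) = 75.5%.

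**Step 3: share of variance due to type.** R² = p(1 − p) × gap² / SD², with p the share of simple UTI. At p = 0.4:

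| Gap | R², A | R², B |
|---|---|---|
| 2 days | 0.24 × 4/25 = 0.04 | 0.24 × 4/16 = 0.06 |
| 4 days | 0.24 × 16/25 = 0.15 | 0.24 × 16/16 = 0.24 |

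**Step 4: power of the rank tests by simulation** (100 per arm, normal outcomes, constant effect, 4,000 replicates). The simple share is 40%, except in the no-gap row, where it is 50%.

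| Gap | A, Mann–Whitney | A, van Elteren by type | B, Mann–Whitney | B, van Elteren by type |
|---|---|---|---|---|
| none | 79.3% | 78.9% | 72.9% | 72.5% |
| 2 days | 78.8% | 79.8% | 72.7% | 74.8% |
| 4 days | 79.2% | 85.1% | 73.2% | 84.8% |

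The Monte Carlo standard error is about √(0.8 × 0.2/4000) = 0.6 point. Over 30 to 50% simple UTI, the gain at a 2-day gap is about 0.5 to 2.5 points. At a 4-day gap it is about 5 to 7 points (A) and 9 to 13 points (B). Under the null the rejection rates were 4.5 to 5.3%, with or without stratification.

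**Step 5: effect confined to one type.** Suppose the B effect is 2.5 days in febrile UTI and none in simple UTI (average 0.6 × 2.5 = 1.5 days). Stratifying then gains nothing at a 2-day gap (74.1% versus 73.9%) and less at a 4-day gap (76.9% versus 81.7%).

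**Step 6: more strata.** Adding the other intervention's assignment to the strata changed power by 0 to 1.4 points downward when that factor had no effect on the outcome. A 1-day effect of that factor explains only 1²/4/25 = 0.010 (A) or 1²/4/16 = 0.016 (B) of the variance. Eight strata (simple/febrile × complicated/uncomplicated × other arm) cost about 2 to 3 points against type alone. With gaps of 0 to 2 days they lose up to 3 points against the unstratified test.

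**Step 7: chance imbalance.** At a 50/50 mix the SD of the between-arm difference in type share is √(2 × 0.5 × 0.5/100) = 0.071, and the 95% range is ±1.96 × 0.071 = ±0.14. With a 4-day gap the crude difference moves by up to 4 × 0.139 = 0.55 day, against targets of 2 and 1.5 days.

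**The case against.** The strongest reply is that nothing is broken. In a 1:1 randomized trial an unstratified Mann–Whitney test holds its level, chance imbalance is already in its null variance, and the sample sizes were computed for an unadjusted comparison. All of that stands.

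It can also be said that a condensed article leaves model details to a fuller document. That is fair for the randomization lists and for unnamed terms in the median regression, so the absence of any described stratified randomization is no fault. It does not cover this point, because the article names the test and assigns UTI subgroup to an exploratory step.

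Some stronger readings are tempting but not supported:

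- *The primary result is biased, or UTI type is ignored altogether.* Neither holds. The test is valid, and UTI subgroup is in the second-step model.
- *A pooled effect is uninterpretable where the biomarkers are not used.* The Abstract defines A as a protocol built on UTI type, PCT and pyuria, and B as ProADM within an assessment bundle. The pooled contrast answers that strategy question.
- *Stratified analysis removes chance imbalance.* It adjusts for imbalance in that factor and does not prevent it.
- *The gain is large and certain.* A 6-day gap might be inferred by setting a single dose against at least 7 days. But simple UTI also has a twice-daily option whose duration is not visible, since Figure 2 is not shown. No gap can be derived from the article.
- *The rank test must also be stratified by the other intervention.* The article does not expect this to matter, citing earlier work in which "shorter duration of antibiotic therapy in LRTIs did not influence the overall length of stay". The assignments are independent, and the interaction regression needs both factors anyway.

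**Conclusion.** The point holds as one of efficiency. The primary rank test leaves out a prognostic variable that is definable at presentation and that the article ties to both primary endpoints.

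The gain from including it is conditional on the unknown gap between types. It runs from a loss of under 1 point of power with no gap, through a small gain at 2 days, to about 84–85% (A) and 82–85% (B) at 4 days. These figures assume 100 evaluable per arm, 30 to 50% simple UTI, normal outcomes and a constant effect; the gain shrinks or vanishes if the effect sits in one type. The possible benefit is greater for B, which starts from lower power. Because the worst case is a fraction of a point, the change is worth making, but leaving it out would not invalidate the trial.

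**What to change.** - Make the primary test for each endpoint a van Elteren test with two strata: simple versus febrile UTI, as defined under Definitions and recorded before randomization. State that the final upper/lower classification under Measurements is not used for this, because it draws on biomarker levels, ultrasound and the urinary protein profile.
- Put the same term in the primary median regression, and report estimates by type as supportive.
- Do not stratify the rank test further by complicated status or by the other intervention. The other assignment belongs in the median regression, where the interaction test already needs it.
- Keep time to reach stability out of the primary model, since it is observed after randomization.

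The cost is a few sentences in the analysis plan, fixed before outcomes are compared by arm, slightly more analysis work, and under 1 point of power if the types turn out not to differ. The presenting signs that define the type are already needed to apply the algorithms.

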**Figure 4 F4:**
[figure not shown]
**Risk assessment during hospitalization - site-of-care decisions (ProADM on day 3).** ICU: intensive care unit; PACD: post-acute care discharge score; SPI: *Selbstpflegeindex* self-care deficit score; UTI: urinary tract infection.

Levels of ProADM are measured on admission and on day 3. ProADM cutoff tertiles derived from patients with LRTI will be used for severity assessment [41]: <0.75 nmol/l; 0.75 to 1.5 nmol/l; >1.5 nmol/l. Physicians receive detailed information on how to interpret ProADM cutoffs and about the results from previous trials when ProADM was used in patients with LRTI [12,29,31,34,35,49-51]. ProADM is measured in an ethylenediaminetetraacetic acid (EDTA) plasma by a sandwich immunoassay (MR-ProADM, BRAHMS AG, Hennigsdorf, Germany) with an analytical detection limit of 0.08 nmol/l and a functional assay sensitivity of 0.12 nmol/l. It is available within 1.5 h upon ordering (24 h a day, daily).

Reassessment of the possibility for discharge from the acute-care hospital is based upon reaching medical stability at any time plus appropriate ProADM levels with particular emphasis on assessment on day 3 (Figure 4). On day 3, the treating physicians receive recommendations regarding discharge according to the clinical stability algorithm. Guidelines are displayed on handouts given to the treating physicians. Algorithm compliance is controlled by the study team and reasons for non-compliance are documented.

Discharge planning based on the biopsychosocial risk at admission (PACD ≥ 8) is initiated immediately and any need for action discussed at each round.

Patients with low medical risk or medically stabilized but high biopsychosocial requirements can be triaged to nurse-led care. The nursing staff is in charge of further management with medical input only at further request or if there is a medical deterioration.

Medically stable patients not fulfilling medical criteria and biopsychosocial, functional and organizational overruling criteria (see section “Overruling criteria for antibiotic treatment and hospitalization”) are considered suitable for discharge to home. Patients meeting biopsychosocial or functional overruling criteria and organizational criteria (waiting for a transfer to the non-acute setting) are referred to non-acute medical care (nurse-led care, health resort, rehabilitation, transitional care or long-term care) (Figure 4).

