### Outcomes and adverse events

The primary endpoint for Intervention A is overall exposure to antibiotics in the PCT and pyuria guidance group compared to the control group. Endpoints are assessed at discharge from hospital, and 30 and 90 days after admission. As secondary endpoints, we will compare the PCT-pyuria group with the control group regarding:

A. Clinical and microbiological cure 7 days after end of therapy.

B. 30-day rate of clinical and microbiological recurrence.

C. 90-day rate of clinical and microbiological recurrence.

D. Antibiotic-associated side effects.

Regardless of group assignment, we will investigate:

E. The relationships of pyuria, urine culture cutoffs and urinary α1-microglobulin/creatinine ratio with the presence of pyelonephritis and level of biomarkers (CRP, PCT, ProADM, and other biomarkers such as urea, natriuretic peptides (ANP, BNP), copeptin, endothelin, apoprotein A1).

F. Correlation between sonographic signs of pyelonephritis and diagnosis based on urine culture cutoffs, clinical criteria and biomarkers.

Our hypothesis for the secondary endpoints A to C is that there is no difference between the two study groups. Our hypothesis for endpoints E and F is that urinary markers and contrast-enhanced ultrasound correlate with systemic biomarkers and diagnosis of pyelonephritis.

For the primary endpoint for Intervention B, we assess the length of physician-led hospitalization in the ProADM-guided triage group compared to the control group within a follow-up of 90 days. As secondary endpoints, we will compare the ProADM group with the control group regarding:

A. resource utilization, defined as the length of index hospitalization (physician- and/or nurse-led); rate and length of re-hospitalization; rate of general practitioner visits; rate of medical investigations and interventions related to UTI and overall, rate of treatment changes related to UTI, for example, antibiotic escalations. The hypothesis is that there are no excess re-hospitalizations or visits to the GP while there are fewer treatment changes and medical investigations in the ProADM group.

B. Proportion of patients triaged according to the risk assessment bundles. The hypothesis is that physician adherence to site-of-care decisions will be 20% higher in the intervention group.

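### Two supportive analyses of the primary endpoints are badly specified: the per-protocol adherence rule covers triage only, and a post-randomization variable is listed as a confounder

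*Protocol article*

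**What the plan says.** All the analysis rules are in the protocol article under Statistical considerations. The primary population is the full analysis set by intention to treat, with a Mann–Whitney test and a median regression for each co-primary endpoint (antibiotic duration for A, length of physician-led stay for B). Two further analyses are at issue.

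- **Per-protocol set.** "A secondary analysis population, the per-protocol population, will be defined, which excludes major protocol violators". There are three grounds for exclusion. The first is "violation of inclusion or exclusion criteria". The second is treatment not according to the trial requirements, spelled out in parentheses as "overriding of triage recommendations on admission or on day 3 without a pre-specified reason". The third is loss to follow-up. The primary analysis is then repeated on this set, with no restriction to one endpoint.
- **Second-step model.** "In a second step, the primary endpoint will be explored for association with potential prognostic factors in a median regression model", taking account of "potential confounding factors such as: age, sex, UTI subgroup, time to reach stability", followed by co-morbidities, patient preferences and prior living conditions.

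Two other places bear on these. Under Intervention B, "Reassessment of the possibility for discharge from the acute-care hospital is based upon reaching medical stability at any time", together with ProADM levels. Under Outcomes and adverse events, a secondary hypothesis for B is that "physician adherence to site-of-care decisions will be 20% higher in the intervention group".

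**The concern.** A per-protocol repeat is meant to show what happens when the assigned strategy is followed. Triage is the subject of Intervention B. A set whose only adherence test is triage does not answer that question for Intervention A, yet A's endpoint is analysed on it too.

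A confounder of a randomized comparison would have to be a common cause of allocation and outcome. Time to stability arises after allocation, under open-label care, and feeds into the decision to discharge. If the arm changes it, adjustment removes that part of the effect. If an unmeasured factor such as severity drives both stability and stay, adjustment adds a further distortion. Patient preferences raise the same question if recorded after allocation.

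At stake is the reading of these supportive results. A per-protocol figure for A could be quoted as an adherence result when it is not one, and an adjusted arm effect could be set against the primary result.

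**Working it through.** **Planned effects, for scale.** Inputs from Sample size: A, 10 vs 8 days, SD 5; B, 6 vs 4.5 days, SD 4; 80% power, 5% alpha (two-sided assumed). With n per arm = 2(1.960 + 0.842)² × SD²/Δ²:

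- A: 2 × 7.849 × 25/4 = 98.1, so 99.
- B: 2 × 7.849 × 16/2.25 = 111.6, so 112.

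Both stated figures reproduce and neither is disputed. The yardstick for B is 1.5 days.

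**Per-protocol rule applied to endpoint A.** For patients who are eligible and followed up:

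| Antibiotic strategy for the assigned arm | Triage recommendation | Stated rule | An adherence set for A would |
|---|---|---|---|
| followed | followed | keeps | keep |
| followed | overridden, no pre-specified reason | removes | keep |
| not followed | followed | keeps | remove |
| not followed | overridden, no pre-specified reason | removes | remove |

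The second and third rows are wrong for A. No assumption about rates is needed.

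**Adjusting for time to stability.** The documents give no mediated share, so these are assumptions: T = arm, U = unmeasured severity (variance 1), m = mediated share.

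- Time to stability: S = 3 + aT + U + error (SD 1.5), with a = -1.5m/0.8.
- Stay: Y = 3.6 - 1.5(1 - m)T + 0.8S + cU + error (SD 3).
- Total effect: -1.5(1 - m) + 0.8a = -1.5 for every m.
- Given S and T, the expected U is λ(S - 3 - aT), with λ = 1/(1 + 1.5²) = 0.308.
- Arm coefficient after adjusting for S: -1.5(1 - m) - cλa.

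| m | Formula, c = 0 | Simulated | Formula, c = 1.5 | Simulated |
|---|---|---|---|---|
| 0 | -1.50 | -1.54 | -1.50 | -1.54 |
| 25% | -1.13 | -1.13 | -0.91 | -0.89 |
| 50% | -0.75 | -0.76 | -0.32 | -0.29 |
| 100% | 0 | +0.01 | +0.87 | +0.85 |

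Example, m = 50%, c = 1.5: a = -0.9375, so -0.75 + 1.5 × 0.308 × 0.9375 = -0.32. The simulated values are median regressions on 100,000 patients; without the adjustment they gave -1.43 to -1.56.

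**Per-protocol exclusions for B.** Assumptions: SD 4; override probability depends on severity; the adherence hypothesis is read as a 20-point gap in excluded overrides (10% vs 30%, 20% vs 40%, 30% vs 50%, higher in control). Differences in median stay, ProADM minus control, 400,000 patients:

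| Overrides more likely in | True 0 | True -1.5 |
|---|---|---|
| sicker patients | +0.30 to +0.33 | -1.18 to -1.17 |
| less sick patients | -0.33 to -0.30 | -1.83 to -1.81 |
| either, equal 20% rates | 0.00 to +0.02 | -1.51 to -1.49 |

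The shift is about 0.3 day, or 0.3/1.5 = 20% of the planned effect, in either direction. It vanishes when override rates and selection are the same in both arms.

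**The case against.** The strongest reply is that neither analysis carries the conclusion. The per-protocol set is called secondary and its use a sensitivity analysis, which is common practice beside intention to treat. The second-step model is described as exploring prognostic factors and need not report an arm effect; time to stability can legitimately appear in a descriptive prognostic model. All of this stands, and it limits the point to supportive analyses.

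Mediation is also not shown. Stability preceding discharge makes it a cause of stay; it mediates only if the arm changes it. Intervention B changes admission criteria and adds ProADM to the discharge decision, while the standardized stability assessment and care bundle apply in both groups. The effect could run largely around stability, and the first row of the mediation table would then apply. This stands too.

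For B, overrides with a pre-specified reason are not exclusions, and the article lists many overruling criteria. If those are the reasons meant, exclusions may be few. The adherence hypothesis concerns adherence overall, and does not say whether 20% is absolute or relative; 20% of a control adherence p is a gap of 0.2p, less than 20 points.

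Three stronger readings are tempting and not supported. A reader might infer that triage overrides alone define the per-protocol set, but eligibility violations and loss to follow-up also exclude ("without a pre-specified reason) or lost to follow-up"). A reader might infer that both analyses necessarily give biased effects, but bias depends on quantities the article does not give. A reader might infer that unequal exclusions must favour the ProADM arm, but the direction depends on who is overridden.

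What the reply does not remove is the mismatch for A. It could be said that the general phrase about trial requirements already covers the antibiotic algorithm. But the parenthesis that follows is worded as a definition, not as an example, and names triage only. Nor does the exploratory purpose make a post-randomization variable a confounder.

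**Conclusion.** The point holds for two supportive analyses and should be corrected; the primary intention-to-treat comparison is untouched.

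The mismatch for Intervention A follows from the text alone: applied as written, the rule does not select patients by adherence to A. How many patients it misclassifies cannot be stated, since the article gives no rates.

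Listing time to stability as a confounder is wrong as a label, and harmful only if an arm effect is read from that model and the arm affects stability. The result then ranges from no change, through the attenuated values at 25% and 50% mediation, to zero or a reversed sign at full mediation. The slope of 0.8, the severity factor and the mediated shares are all assumed.

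For B, the article's own hypothesis of higher adherence in one arm is reason to call the per-protocol result supportive. The shift of about 0.3 day rests on an assumed 20-point gap and severity-related overrides, and is not a prediction.

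**What to change.** 1. In any model that reports an arm effect, use baseline covariates only. Drop time to stability and any patient preference recorded after allocation, or keep them in a purely descriptive prognostic model without an arm effect.
2. Define two per-protocol sets: for A, by adherence to the assigned antibiotic algorithm or guideline duration; for B, by adherence to the triage recommendation, with the present allowance for pre-specified reasons. Keep eligibility violations and loss to follow-up as exclusions in both.
3. Report the number of exclusions and the reasons by arm for each set.
4. State that the per-protocol results are supportive. Separate sets repair the mismatch for A but do not remove selection by adherence, least of all for B.

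The cost is a change of wording and a little more analysis. It is not quite wording alone for A: documentation of reasons for non-compliance is described only under Intervention B, while Measurements says only that compliance is reinforced by assigned group. Adherence to A would have to be derived from the recorded antibiotic data.
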